### Interim analyses {21b}

Formal interim analysis of the primary and secondary outcomes is not applicable in this trial.

### Methods for additional analyses {20b}

Subgroup analyses of the primary and secondary outcomes stratified by variables as follows: gender (male and female) and age group (< 75 years old, ≥ 75 years old). Adjusted GLMMs will be utilized in each subgroup to ensure that the effects observed in subgroups are adjusted for the same confounders as in the general analysis.

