## Statistical methods

### Statistical methods for primary and secondary outcomes {20a}

Statistical analysis will be conducted using R (version 4.2.0; R Foundation for Statistical Computing). We will use a two-sided significance level of 5% and report the results with two-sided 95% confidence intervals (CIs) for all statistical analyses. For continuous variables, the Shapiro-Wilk test and Levene’s test will be utilized to identify the appropriate data treatment (i.e., parametric or non-parametric analysis), followed by a descriptive analysis presenting as means (SD) or median (IQR). Categorical variables will be presented as frequencies (percentages). For the statistical analysis of repeated outcome measures, generalized linear mixed models (GLMMs) will be used. These models are well-suited for our study design as they can effectively handle the complexities of repeated measures data and accommodate various response variable distributions, including normal, nonnormal, and ordinal categorical responses [37–39]. The primary fixed effects in our models will be the intervention and the time. To account for individual variability among participants, random effects will be included in the model to capture the individual variation. We will adjust for potential confounders that might influence the relationship between the intervention and the outcomes. These confounders include both basic demographics (age, gender, and education level) and heatlh-related factors (physical activity level, diet, smoking status, and medication use). We will further consider the inclusion of interaction terms in our model to examine if the effect of the intervention varies across different levels of confounders.

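### The subgroup plan commits only to separate models within gender and age strata, which do not test whether the effect differs; the interaction test is optional and not tied to these subgroups

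*Protocol article*

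**What the plan says.** Two sections of the protocol article bear on this.

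- **Methods for additional analyses {20b}.** The scope is "Subgroup analyses of the primary and secondary outcomes stratified by variables as follows", and the factors are "gender (male and female) and age group (< 75 years old, ≥ 75 years old"). The method is "Adjusted GLMMs will be utilized in each subgroup", and the reason given is that every stratum effect should carry the main model's adjustment. The section names no comparison between strata.
- **Statistical methods {20a}.** After describing the main mixed model, the article adds: "We will further consider the inclusion of interaction terms in our model". The stated purpose is to see whether the effect depends on the level of a confounder. The confounder list includes "basic demographics (age, gender, and education level"), so both subgroup variables are on it. The sentence does not mention the cut at 75 years or the subgroup analyses. The same section sets a two-sided 5% level and 95% confidence intervals for all analyses.

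The plan for assessment of outcomes {18a} adds that system usability and satisfaction are measured only in the intervention group.

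**The concern.** A subgroup analysis asks whether the intervention works differently in men and women, or in younger and older participants. Two models fitted separately give two effects, two confidence intervals and two p-values, but no estimate of the difference between the effects and no interval for it. The plan's firm commitment is to these separate models. The analysis that would answer the question is left to discretion, and it could be included or dropped after the stratum results are known.

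Without a stated basis for comparison, a reader may take significance in one stratum and not the other as evidence that the system helps only one sex or one age group. With the 150 participants split, that pattern is common even when the true effect is the same in both strata.

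**Working it through.** **The plan's own figures.** The plan gives no figure for the subgroup analyses. The nearest is the power statement in Sample size {14}: two-sided α = 5%, power 0.80, δ = 2.3, σ = 6.12, k = 3, ρ = 0.7, 60 per arm. The printed formula gives 2 × (1.960 + 0.842)² × 6.12² / (3 × 2.3²) = 37.05, so 38 per arm rather than 60. The attrition step does reproduce: 120 / (1 − 0.20) = 150. The gap between 38 and 60 is a separate matter, but because of it I did not rely on 80% overall power alone.

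**Assumptions.** Stratum shares are not given, so I used 50:50 to 80:20. The true effect is identical in both strata, the strata are independent, and clustering by site is ignored.

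**Formulas.** Let T be the overall non-centrality (true effect divided by its standard error). A stratum holding a share f of participants has non-centrality T√f and power p ≈ Φ(T√f − 1.960). The chance that exactly one of two strata is significant is p₁(1 − p₂) + p₂(1 − p₁).

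**Overall power 80%**, T = 1.960 + 0.842 = 2.80:

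- 50:50: 2.80 × √0.5 = 1.98, power 0.508 in each stratum; 2 × 0.508 × 0.492 = 0.50.
- 70:30: powers 0.650 and 0.335; 0.650 × 0.665 + 0.335 × 0.350 = 0.55.

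**Other overall powers**, entering 60 per arm:

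- Printed formula (variance σ²/k): T = 2.3 / (6.12/√3 × √(2/60)) = 3.57, overall power 95%.
- Mean of k equally correlated measures (variance σ²(1 + 2 × 0.7)/3): T = 2.3 / (6.12 × √0.8 × √(2/60)) = 2.30, overall power 63%.

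Chance that exactly one stratum is significant under an identical true effect:

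| Overall power | 50:50 | 60:40 | 70:30 | 80:20 |
|---|---|---|---|---|
| 63% | 47% | 47% | 49% | 53% |
| 80% | 50% | 51% | 55% | 61% |
| 95% | 41% | 43% | 50% | 61% |

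With no effect at all, the figure is 2 × 0.05 × 0.95 = 9.5% per factor.

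**Interaction test.** Under an identical effect it gives a false difference in 5% of trials per factor. For at least one of two factors, if independent, it is 1 − 0.95² = 9.75%.

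**Its power.** With equal strata the standard error of the between-stratum difference is twice that of the overall effect. A difference as large as the overall effect then has non-centrality 2.80 / 2 = 1.40 and power about 29%.

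**The case against.** The strongest reply is that the plan does foresee a test of heterogeneity. The interaction sentence in {20a} covers confounders that include age and gender, so a reader who infers that the plan has no interaction analysis would be wrong. That stands. What remains is that the sentence promises only consideration, and nothing connects it to {20b} or to the age cut.

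A second reply is that no rule for comparing p-values is written anywhere. The reason given for the stratum models is consistent adjustment, and confidence intervals are promised throughout. Adjusted stratum estimates with intervals are a legitimate display and do not by themselves create a false difference. Re-estimating covariates within strata costs precision but is not an error. This also stands, and it makes the percentages conditional.

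Third, the arithmetic ignores that both strata are drawn from the same six randomised sites. Shared site effects would correlate the stratum estimates positively and tend to lower the discordance, and power would not fall simply with the square root of the share. The protocol gives no intracluster correlation, so I cannot quantify this.

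Finally, a journal article may leave the formal comparison of strata to an analysis plan. Silence alone would be no finding. Here, however, the article does fix a method for the subgroups, and the method it fixes does not answer the subgroup question.

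**Conclusion.** The point holds in a limited form. The only committed subgroup method does not test whether the intervention effect differs by gender or age group, and the valid test is optional and detached from those subgroups.

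If differences were read from significance in one stratum and not the other, an identical true effect would produce that pattern in roughly 40% to 60% of trials, against 5% for an interaction test. This rests on the assumed shares and powers, on independent strata, and on clustering being ignored.

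A reader might infer that the trial will often report a spurious subgroup difference. The document does not support that, because it states no such decision rule. The subgroup analyses are additional analyses and do not affect the primary comparison. This is a cheap improvement.

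**What to change.** In {20b}, replace the separate stratum models as follows.

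- **Outcomes measured in both arms (DDS, CDGI-E).** For gender and for age group (cut at 75), fit a model on all participants with intervention-by-subgroup and intervention-by-subgroup-by-time terms, keeping the main model's covariates and random effects. Report the interaction with its 95% CI as the only basis for claiming that the effect differs. Take the stratum estimates and intervals from the same model and label them exploratory.
- **Outcomes measured only in the intervention group (usability and satisfaction).** No intervention-by-subgroup term can be fitted, so give stratum summaries descriptively.
- **Statement in {20a}.** Replace "We will further consider the inclusion of interaction terms in our model" with a commitment to these specified interactions, cross-referenced to {20b}.

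The cost is wording and a few model terms per factor; with three time points the three-way term alone adds two coefficients. The interaction test will have low power, about 29% for a difference as large as the overall effect under the assumptions above. The plan should say so, and should say that a non-significant interaction does not show equal effects.

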### Methods in analysis to handle protocol non-adherence and any statistical methods to handle missing data {20c}

Both intention-to-treat analysis (ITT) and per-protocol (PP) analysis will be conducted. Specifically, the interpretation of the intervention effect would be more likely to consider ITT as the gold standard approach. However, both ITT and PP analyses will be reported alongside each other for comparison. To conduct ITT analysis with incomplete data, missing data will be imputed using multiple imputation techniques.

### Plans to give access to the full protocol, participant-level data, and statistical code {31c}

The individual-level dataset and statistical code generated during the current study will be available from the corresponding author upon reasonable request after 5 years since the trial is finished.

## Oversight and monitoring

### Composition of the coordinating center and trial steering committee {5d}

A trial steering committee and a data monitoring committee have been established to oversee the trial. The steering committee consists of investigators, information scientists, and nutrition scientists from Medical Information Institution of the Chinese Academy of Medical Sciences, Chinese Center for Disease Control and Prevention, and Peking Union Medical College Hospital. The main responsibility of the steering committee is to evaluate the protocol to improve its feasibility and make necessary amendments to address ethical concerns. They also guide the planned interventions for the targeted elderly population.

### Composition of the data monitoring committee, its role and reporting structure {21a}

The data monitoring committee (DMC) comprises data scientists and statisticians from Peking Union Medical College. Their primary responsibility is to ensure the data quality of the study by conducting audits of the trial every 3 months. The DMC operates independently of the sponsor with no competing interests. The committee charter is subject to further review upon request from the corresponding author.

### Adverse event reporting and harms {22}

Adverse events in this trial include deaths, emergency room visits, onset of cognitive impairment, onset of physical dysfunction, and hospitalization lasting longer than 24 h. The investigators will collect and record the adverse events at the end of the study and then examine the association between their incidence and the health conditions of elderly individuals.

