### Sample size {14}

This study uses a randomized, non-blinded, two-armed study design with three times measurements during the study. The power calculation is based on the primary outcome measure- dietary diversity score. The sample size was calculated according to the repeated-measures formula [24, 25]: *N* = $$\frac{2{({{\text{Z}}}_{1-\mathrm{\alpha }/2}+ {{\text{Z}}}_{1-\upbeta })}^{2} {\upsigma }^{2}}{k{\updelta }^{2}}$$. In this formula, parameters denoting the number of repeated times *k* = 3, type I error rate *α* = 5% (two-sided), and a power level of 0.80. We set the smallest detected meaningful difference *δ* = 2.3 according to experts’ experience. Based on the results of relevant studies and our baseline survey, the correlation coefficient among measures *ρ* = 0.7, and equal standard deviation *σ* = 6.12 was used [24, 26]. It was estimated that the desired number of included participants at baseline should be set at a minimum of 60 for each arm. Consequently, a total of 150 community-dwelling elderly individuals are expected to recruit at baseline considering an attrition rate of 20% [27–29].

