## Data collection and management

### Plans for assessment and collection of outcomes {18a}

All primary and secondary outcomes will be repeatedly measured at baseline, 3 months, and 6 months. System usability and satisfaction will only be evaluated in the intervention group, while dietary behaviors (dietary diversity and diet quality, adherence to the interventions), nutritional status, and anthropometric measurements will be evaluated in both the intervention and control groups. Detailed information on data collection methods is shown in Table 2.

**Table 2 Tab2:** The outcome measures and collecting methods

**Outcome measure**		**Collection method**
Dietary behavior	Dietary diversity	IoT system log, DDS
	Diet quality	IoT system log, CDGI-E
	Recommendation adherence	IoT system log
System usability and satisfaction	Satisfaction ratings	Questionnaire (CSAT)
	Ease of use ratings	Questionnaire (CES)
Nutritional status	Risk of malnutrition	Questionnaire (MNA-SF)
Anthropometric measurements	Body mass index	Basic body measurement (body weight scale, height rod)
	Waist circumference	Basic body measurement (measuring tape)
	Systolic blood pressure	Blood pressure monitor
	Diastolic blood pressure	Blood pressure monitor
	Skin folds	Basic body measurement (skinfold caliper)

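### Adverse events are set to be recorded at the end of the study and related to health conditions, so events in participants who leave risk being missed and the one stated analysis does not address a difference between arms

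*Protocol article*

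**What the plan says.** The section Adverse event reporting and harms {22} defines the events: "Adverse events in this trial include deaths, emergency room visits, onset of cognitive impairment, onset of physical dysfunction, and hospitalization lasting longer than 24 h". It then fixes the time of collection: "The investigators will collect and record the adverse events at the end of the study". It also names one use of the data, to "examine the association between their incidence and the health conditions of elderly individuals". The section mentions no other time point, no collection at withdrawal, no source of information and no comparison by arm.

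Other sections bear on this:

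- **Sample size {14}** plans for 20% attrition and recruits 150 people. The Discussion expects that low acceptance of the intervention may lead to high attrition.
- **Plans for assessment and collection of outcomes {18a}** schedules contacts at baseline, 3 months and 6 months: "All primary and secondary outcomes will be repeatedly measured at baseline, 3 months, and 6 months". Adverse events are not in that section's Table 2, nor among the primary, secondary or exploratory outcomes in Outcomes {12}.
- **Plans to promote participant retention {18b}** provides for contact persons and for a tracking system that draws on primary care center records. Both are described as means of keeping up follow-up assessments.
- **Composition of the data monitoring committee {21a}** gives the committee's main task as data quality, with audits every 3 months. No safety review is stated.

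**The concern.** Two choices in {22} work against a sound account of harms.

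The first is timing. Death, a long hospital stay or a new impairment can be the reason someone leaves the trial. If information is gathered once, at the end, the people most likely to have had an event may be the hardest to reach. Participants and researchers are unblinded and the two arms have different contact with the trial, so any under-count could also differ by arm.

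The second is the analysis. An association between events and health conditions shows which participants are frail. It does not show whether events were more frequent with the recommendation system than with lectures alone, which is the harm question that a controlled comparison can address.

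At stake is the completeness and usefulness of the safety record, not the primary result.

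**Working it through.** **Planned losses.** Sample size {14} gives the requirement as follows: "the desired number of included participants at baseline should be set at a minimum of 60 for each arm". Two arms give 120. Inflating for 20% attrition, 120 / (1 − 0.20) = 150, which reproduces the stated total. Expected leavers are 0.20 × 150 = 30, and completers 120. (Section {18b} prints 20% as a retention rate. Its own reference to high attrition suggests that attrition was meant, and 20% attrition is used here.)

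**Share of events at risk.** Let d be the proportion who leave and r the event rate in leavers divided by that in completers. If no leaver's event is recovered, the share of all events missed is

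d·r / [(1 − d) + d·r].

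The documents give d = 0.20. They give no event rates, so r is an assumption, taken from 1 to 3.

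| r (assumed) | Calculation | Share missed |
|---|---|---|
| 1 | 0.20 / (0.80 + 0.20) | 20% |
| 2 | 0.40 / (0.80 + 0.40) | 33% |
| 3 | 0.60 / (0.80 + 0.60) | 43% |

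The completers' event rate cancels, so the shares do not depend on it. As counts, with an assumed 10% rate in completers, 120 × 0.10 = 12 participants with events are seen. The unseen number is 30 × 0.10 = 3, 30 × 0.20 = 6 or 30 × 0.30 = 9, giving 3/15, 6/18 and 9/21.

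For a given r these are upper bounds. If half of the leavers' events were recovered, the shares would halve to 10%, 17% and 21%.

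**Does another section repair the rule?** The 3-month contact in {18a} exists but is assigned to the listed outcomes. The tracking records in {18b} exist but are not linked to adverse events. The statistical methods ({20a} to {20c}) deal with primary and secondary outcomes. The data monitoring committee audits data quality. Nothing shown changes the collection time or adds a comparison by arm.

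**What a comparison by arm could show.** With 75 per arm and an assumed 10% rate in both, the half-width of the 95% confidence interval for the difference is 1.96 × √(2 × 0.10 × 0.90 / 75) = 0.096, or about 9.6 percentage points. Allowance for the six randomised sites would widen it. The estimate would describe the data but could exclude only large differences.

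**The case against.** The best defence is that {22} says when events are recorded, not from whom or from what source.

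- **Are leavers' events lost?** A reader might infer this, but the text does not say it. Collection is not limited to people present at the last visit. Death is on the list and cannot be self-reported, so some other source is implied, and {18b} provides contact persons and primary care records. This stands: the events are at risk of being missed, not shown to be lost.
- **Is the end of the study the sole collection point?** That is the plain reading of {22}, but the SPIRIT schedule and the timeline figure are not shown and might say more.
- **Is a comparison by arm impossible or excluded?** A reader might infer this too. Events recorded per participant can be tabulated by arm, naming one analysis does not forbid another, and an unseen analysis plan may include such a table. What stands is narrower: the one analysis that the protocol states does not address the arms. An analysis plan could add a table, but it could not restore events that were never collected.
- **Is a stated outcome biased?** No. Adverse events are not a listed outcome, so the schedule in {18a} does not contradict {22}.
- **Is drop-out informative?** The documents attribute the expected attrition to low acceptance and to experience with earlier digital health interventions, not to illness. Event-related leaving is plausible given the listed events, but the plan does not establish it. That is why the case of equal rates is shown first.

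**Conclusion.** The concern holds in a limited form. The protocol itself fixes one late collection time and names one analysis that leaves out the arms, so this is a stated rule and not a detail left to another document. As written, it risks an incomplete count of harms.

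The share missed would be 20% at equal event rates, and 33% to 43% if leavers' rates were two to three times as high. This rests on 20% attrition, on assumed rate ratios and on no recovery of leavers' events. The last condition makes the figures upper bounds for each ratio, not estimates. The direction and size of any difference in under-counting between arms cannot be derived from the documents.

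The rule should be changed, but it does not alter the primary analysis.

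**What to change.** Amend {22} in three respects:

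1. Record adverse events with their onset date at the existing 3- and 6-month assessments and at withdrawal.
2. For participants lost to follow-up, state that the primary care center records already used for tracking under {18b} will also be searched for adverse events.
3. Report the number and proportion of participants with an event by arm, with a between-arm estimate and confidence interval. Acknowledge that these are imprecise with 75 per arm in six clusters. Keep the association with health conditions as a supplement.

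The cost is a few questions at contacts already scheduled, a record search for those lost, one extra table and a short amendment through the route in {25}. Neither the interventions nor the primary analysis changes.

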### Trial design {8}

This experimental study expected to run from July 2023 to September 2024 will follow a non-blinded, paralleled, two-arm pre-test post-test design including 150 community-dwelling elders. This trial will be conducted simultaneously in six community health service centers within Nanhu district, Jiaxing City, located in Zhejiang province, China. Following a cluster randomization design, intervention and control sites will be allocated in a 1:1 ratio based on a randomized allocation sequence generated by a single investigator using R 4.2.0 The intervention period is expected to last for 6 months, following a preparation and recruitment phase. Effect measurements will be conducted at three time points: at the beginning, after 3 months, and after 6 months of the intervention. Implementation measurements will be carried out throughout the study. The trial design follows the SPIRIT checklist (Additional file 1).

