### Data management {19}

In this trial, assessment data will be collected through two methods: (1) an IoT-based ambient dietary behavior tracking system and (2) face-to-face evaluations. The assessment data will be electronically saved in an encrypted database and deidentified, with access granted only to researchers designated to control data quality and perform data analysis. Other investigators will only have read permission for the database. Double data entry and logic checks will be conducted to identify any suspicious submissions. Any suspected data errors or items with abnormal values will be logged and excluded from the final analysis. If necessary, investigators will make attempts to re-collect missing static data, such as sociodemographic and medical history. The entire process of data entry, recoding, auditing, and storage will be logged in documents, which are available from the corresponding author upon reasonable request.

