### Frequency and plans for auditing trial conduct {23}

The trial conduct will be audited by DMC every 3 months. The auditing process will be conducted independently of both the investigators and the sponsor.

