## Trial status

This study protocol was approved on August 20, 2023, and this manuscript details the protocol in the original version. The first participant was enrolled on August 21, 2023, and recruitment is expected to be completed by October 19, 2023.

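### Adverse events are collected and recorded only at the end of the study, so events in the first 3 months are ascertained about 3 to 6 months late, although a 3-month assessment already exists in both arms

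*Protocol article*

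**What the plan says.** The section on adverse event reporting and harms {22} lists five event types: death, emergency room visit, onset of cognitive impairment, onset of physical dysfunction, and hospital stay of more than 24 hours. It then sets the timing: "The investigators will collect and record the adverse events at the end of the study". The stated use is to relate the incidence of these events to participants' health conditions.

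The trial design section {8} gives the visit schedule: "Effect measurements will be conducted at three time points: at the beginning, after 3 months, and after 6 months of the intervention". The plan for outcome assessment {18a} applies these time points to both arms for dietary behaviour, nutritional status and anthropometry. Data management {19} names two routes of data collection: "an IoT-based ambient dietary behavior tracking system and (2) face-to-face evaluations".

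On oversight, the article says of the data monitoring committee (DMC): "Their primary responsibility is to ensure the data quality of the study by conducting audits of the trial every 3 months". The auditing section {23} repeats the interval: "The trial conduct will be audited by DMC every 3 months".

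**The concern.** Both collecting and recording are tied to one late point, so the article states the timing and does not leave it open. Participants are over 65, and people with diabetes, hypertension or hyperlipidemia are eligible.

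Three things are at stake.

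- **Late ascertainment.** Early events have to be reconstructed from memory or records, months afterwards.
- **Missed events.** Someone who has died cannot answer at the end, someone newly impaired is a poor informant, and someone who has withdrawn may not be there. Death and cognitive impairment are themselves on the list.
- **No running record.** If nothing is recorded until the end, an audit that falls inside the intervention has no adverse event records to check.

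**Working it through.** There is no stated figure to reproduce. The check compares the collection time with the rest of the schedule and then works out the delay.

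**Step 1: does any other section supply earlier capture?**

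- Trial design {8} and outcome assessment {18a}: visits at 0, 3 and 6 months for effect and outcome measures. Adverse events are not mentioned.
- System usability and satisfaction: monthly questions, in the intervention arm only, on satisfaction and ease of use.
- Retention {18b}: a tracking system that draws on surveys and primary care center records, for scheduling and retention. It could help recover events but is not assigned that task.
- DMC {21a} and auditing {23}: data-quality and conduct audits every 3 months. No adverse event collection is described.

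None does.

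**Step 2: delay from event to record.** Let *t* be the month of the event, counted from the start of the intervention. Delay = collection time − *t*.

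*Reading A, the 6-month assessment:* delay = 6 − *t*. For *t* = 0 it is 6 months and for *t* = 3 it is 3 months. Events in the first 3 months therefore wait 3 to 6 months. If the one-month tracking period follows baseline, counting from baseline adds up to 1 month.

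*Reading B, the last participant's 6-month assessment:* the Trial status section says "The first participant was enrolled on August 21, 2023, and recruitment is expected to be completed by October 19, 2023". Six months after 19 October 2023 is 19 April 2024. From 21 August 2023 that is 242 days / 30.44 = 8.0 months for the first participant enrolled, and 6.0 months for the last.

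*Reading C, the calendar end:* "This experimental study expected to run from July 2023 to September 2024". The day is not given; assume 1 to 30 September 2024.

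| Counted from | To 1 Sep 2024 | To 30 Sep 2024 |
|---|---|---|
| 21 Aug 2023 (first enrolment) | 377 / 30.44 = 12.4 months | 406 / 30.44 = 13.3 months |
| 19 Oct 2023 (planned recruitment close) | 318 / 30.44 = 10.4 months | 347 / 30.44 = 11.4 months |

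Readings B and C count from enrolment, and the intervention follows a preparation and recruitment phase, so part of these intervals may precede it.

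**Step 3: delay if the existing visits are used.** For *t* up to 3, delay = 3 − *t*. For *t* from 3 to 6, delay = 6 − *t*. The maximum is 3 months in both cases.

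**Step 4: who could be missed through dropout.** The sample size section gives the allowance: "a total of 150 community-dwelling elderly individuals are expected to recruit at baseline considering an attrition rate of 20" per cent. 150 × 0.20 = 30 participants, or 75 × 0.20 = 15 per arm with equal arms. This is a planning ceiling on the people affected, not a count of lost events. The article gives no event rate, so no expected number of missed events can be calculated.

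**The case against.** The strongest reply is that the sentence may describe compiling events for analysis, since it goes straight on to the planned association. On that view it does not stop site staff from noting a death when they hear of it. A condensed article may also leave site logging and safety reporting to the full protocol, and the DMC charter is not shown. This stands in part: one cannot infer that the trial has no safety reporting or escalation route, and the point does not claim it. But the sentence gives one time for both collecting and recording, and nothing else in the article modifies it. Informal awareness would also be uneven, because the intervention arm has more staff contact.

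A second reply is that records can recover deaths, emergency visits and hospital stays, that the contacts held for retention can help trace dropouts, and that the planned analysis needs incidence rather than onset dates. Most of this stands. Baseline screening with the MMSE would even allow retesting for cognitive impairment at 6 months in those still present. The difficulty in dating gradual onset is therefore not a ground for the point. What remains is incomplete ascertainment, since the section assigns neither records nor contacts to this task.

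A third reply is that the risk is low: recommendations are advisory, choice is free, and people on strictly mandated diets are excluded. That is right and limits the weight of the point.

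**Conclusion.** The concern holds in a modest form. As written, adverse events in the first 3 months are ascertained about 3 to 6 months later if the end of the study is the 6-month assessment, and later under any calendar reading. Some events in participants who die, become impaired or withdraw may be missed, and the article plans no adverse event record during the intervention. The timing should be changed, but the primary and secondary analyses do not depend on it.

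A reader might infer more than the article supports:

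- *That every early event waits 6 months or longer.* On the 6-month reading, only an event at the very start waits that long.
- *That the delay is 11 to 13 months.* The 11.4- and 13.3-month figures rest on an assumed collection day of 30 September 2024, and the longer one counts from first enrolment, which may precede the intervention.
- *That data on 30 participants will be lost.* That is the attrition allowance, and some of their events could be recovered.

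The conclusion assumes that the harms section is followed literally and that no document outside the article sets an earlier collection time.

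**What to change.** Amend the adverse event section {22} so that the five listed event types are recorded in both arms when they become known, at withdrawal, and at the latest at the existing 3- and 6-month assessments. Use the same fixed questions in both arms at those assessments, because ad hoc logging alone could find more events in the arm with more staff contact. Check reports against primary care records where available. State what the end of the study means. The existing 3-monthly audit would then have records to check during the intervention.

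The cost is a short amendment, a few extra questions at two assessments that already take place, and modest logging by site staff. Listings that reveal the site should be kept from the data analysts, who are to be blinded to assignment.
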